### Concomitant Care Protocol

The aspects related to the concomitant care protocol are as follows:

Permitted: regular medical care, stable chronic disease management, and emergency careProhibited: new sleep medications, sleep clinic consultations, or other sleep apps or programsDocumentation: weekly medication diary and immediate reporting of treatment changesSafety: participants with sleep deterioration (<30 score for >1 week) withdrawn and referredBaseline: usual care patterns documented at enrollment

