### Adherence Assessment

In the experimental group, adherence to personalized recommendations is assessed through self-report at the day 60 closure interview. Participants rate adherence on a scale from 0% to 100% for each recommendation provided. In the control group, adherence to generic sleep hygiene is assessed in a similar manner. Device wear adherence is monitored through objective data. Participants with missing data for >20% of nights may be excluded and replaced.

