### Outcomes

#### Primary Outcome: Mean Samsung Galaxy Watch 4 Sleep Score During the Postintervention Period

We are working within proprietary constraints. We use the Samsung sleep score (1-100 scale) as the primary outcome for the following reasons: (1) real-world relevance: the score is the metric users see and seek to optimize in consumer wearable ecosystems; (2) continuous sensitivity: the scoring scale (1‐100) detects individual-level changes with precision, which categorical systems cannot achieve; (3) composite integration: the score algorithmically combines multiple sleep dimensions (duration, architecture, efficiency, and fragmentation), providing a holistic optimization target; (4) feasibility for personalization: continuous data for 60 nights enable individual ML models to identify predictive patterns; and (5) validation through correlation: secondary PSQI outcomes confirm that objective score improvements correspond to subjective sleep quality perception.

There are some limitations. The use of a proprietary algorithm limits the reproducibility of exact score computation. Moreover, there is no PSG validation of the composite score specifically (though component parameters are validated [36-43]). Furthermore, the manufacturer-specific metric precludes direct cross-device comparisons. These limitations are inherent to consumer wearable research and do not invalidate the personalization methodology (they contextualize the interpretation). Our framework is designed to work *within* these pragmatic constraints while remaining transferable to other manufacturers’ proprietary systems.

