### Blinding (Masking) Level

This is an open-label pilot trial with partial blinding where feasible. Participants become aware of group assignment at different time points (experimental group participants are informed on day 30 at intervention delivery; control group participants are informed on day 60 at close-out). Samsung Galaxy Watch 4 automatically records objective sleep data independent of participant or researcher knowledge, eliminating measurement bias for the primary outcome. The researcher analyzing primary outcome data (Samsung scores) remains blinded to group allocation, and unblinding occurs on day 30 to identify participants for analysis in the experimental group in order to provide personalized recommendations.

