### Data Collection Quality Control

The following measures are implemented for user-related issues: (1) noncompliance: participants with missing data for >20% of nights are excluded and replaced; (2) charging issues: backup chargers are provided, and daily battery monitoring is required; (3) unauthorized modifications: settings are locked, and violations lead to replacement; and (4) sync delays: daily commitment for cloud backup within 24 hours. The following measures are implemented for device-related issues: (1) fragmented recording: nights without combined scores are excluded; (2) data mismatch: nights with artifact conflicts are excluded; and (3) sync errors: multiple attempts are made with escalating intervals. For sensor inaccuracies, quality control is performed through sleep diaries, and outliers trigger replacement. Excluded participants are replaced from the recruitment pool to maintain the sample size. The expected night exclusion impact is around 18%, with anticipated replacement ensuring the target sample.

Subjective data collection is performed through PSQI forms completed on paper. Information is manually entered by the researcher into a password-protected spreadsheet with self-verification (data are entered twice by the researcher to ensure accuracy). Data are processed through the manufacturer’s algorithms to interpret the findings of the 10 explanatory variables and the target variable (Table 1).

**Table 1. T1:** Target and explanatory variables collected by the wearable (indispensable for this study).

Variable		Description	Unit	Data type
Explanatory variable				
sleep_duration		Sum of N1, N2, N3, and REM^a^	Minutes	Integer
movement_awakening		Count of movement during sleep	Number	Integer
sleep_cycle		Count of sleep cycles	Number	Integer
mental_recovery		Score assigned according to the REM phase	Score (0‐100 scale)	Integer
physical_recovery		Score assigned according to the N3 phase	Score (0‐100 scale)	Integer
efficiency		real_total_sleep by sleep_duration	Percentage	Integer
Transition_N1		Sum of minutes of sleep in the N1 phase	Minutes	Integer
Light_N2		Sum of minutes of sleep in the N2 phase	Minutes	Integer
Deep_N3		Sum of minutes of sleep in the N3 phase	Minutes	Integer
REM		Sum of minutes of sleep in the REM phase	Minutes	Integer
Target variable				
sleep_score		Score assigned for the night	Score (1‐100 scale)	Integer

a REM: rapid eye movement.

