### Data Management

Data entered and collected by Samsung Galaxy Watch 4 are automatically synced to Samsung Cloud (encrypted transmission) upon pairing. The PSQI forms are completed on paper, and the information is manually entered by the researcher into a password-protected spreadsheet with self-verification (data entered twice by the researcher to ensure accuracy). All data stored on the researcher’s local computer are encrypted, providing additional privacy protection through local-only storage. Moreover, data are stored in 2 separate local files as a backup measure for protection against file corruption. Access control is set, with only the researcher having access to all study data, including identifiable information linking Participant_ID to personal information. No other personnel have access to the data.

Data security involves (1) physical security (paper PSQI forms are stored in a locked filing cabinet at a secure location), (2) digital security (electronic files are password-protected and encrypted, and are stored on the researcher’s local computer only [no remote or cloud storage of identifiable data]), and (3) transmission security (Samsung device data download uses encrypted protocols [HTTPS]).

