### Ancillary and Posttrial Care

#### Incidental Findings

Participants with incidental findings during the study may be withdrawn and referred for severe sleep deterioration (sleep score <30 for >1 consecutive week). Participants may be withdrawn from the study and referred to sleep medicine services at their medical institutions. Contact information may be provided for sleep specialists in Mexico City. There are no study-related costs for referral (participants use existing health insurance).

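### One safety trigger, set on the primary outcome, has two stated consequences, and the general exclusion rules would normally drop and replace a participant withdrawn early in follow-up because the score was poor

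*Protocol article*

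**What the plan says.** The safety rule appears twice. The Concomitant Care Protocol gives it as a flat consequence: "participants with sleep deterioration (<30 score for >1 week) withdrawn" and referred. Incidental Findings, under Ancillary and Posttrial Care, gives the same threshold, adds that the week must be consecutive, and says that participants "may be withdrawn and referred for severe sleep deterioration". A further sentence there repeats that withdrawal is optional.

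The trigger variable is also the trial's endpoint, headed "Primary Outcome: Mean Samsung Galaxy Watch 4 Sleep Score During the Postintervention Period". Under Blinding (Masking) Level, "unblinding occurs on day 30 to identify participants for analysis in the experimental group". Data Management describes access control "with only the researcher having access to all study data", so the person who sees the scores also knows the arm.

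Four general rules bear on what follows a withdrawal:

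- Data Collection Quality Control, under noncompliance: "participants with missing data for >20% of nights are excluded and replaced". It later adds, without limiting the reason: "Excluded participants are replaced from the recruitment pool to maintain the sample size".
- Adherence Assessment has the softer form: "Participants with missing data for >20% of nights may be excluded and replaced".
- The missing-data sentence at the end of Exploratory Analyses excludes participants without sufficient nights in the baseline and postintervention periods. It gives no threshold. The same paragraph says that the protocol is the complete analysis plan and that no separate one exists.
- Access Control and Protection Layers for Potential and Excluded Participants provides for immediate deletion of data from those who withdraw voluntarily or need to be excluded.

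Harms: Adverse Event Tracking leaves withdrawal events to the informed consent procedures, which are not shown.

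**The concern.** A safety rule should tell the investigator what to do at the threshold. This one is fixed in one section and discretionary in the other. The discretion lies with one person who knows the allocation during follow-up, so two participants in the same state can be handled differently.

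The larger issue is what follows. The trigger is a run of very low values of the endpoint. If crossing it leads to withdrawal, withdrawal to missing nights, and missing nights to exclusion and replacement, a participant leaves the comparison because the outcome was poor. The comparison is then no longer of the groups as randomised. The pilot's main product, an effect size and SD for planning a larger trial, would be affected as well.

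**Working it through.** The plan gives no figure on this point. The nearest is power above 80% at d of at least 1.0 with 16 per arm. It reproduces (0.868, one-sided, noncentral t) and needs no correction here.

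**Step 1: the two consequences.** Same score, same threshold and same duration, apart from the word consecutive. One section says withdrawn, the other may be withdrawn. Neither refers to the other.

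**Step 2: which general rules reach a withdrawn participant.** No rule exempts a safety withdrawal. The 20% rule sits under noncompliance, but the replacement sentence is unrestricted. The insufficient-nights exclusion applies to anyone. The deletion rule names voluntary withdrawal or a need to be excluded. A withdrawal initiated by the researcher fits the second phrase on a natural reading, though it is not named.

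**Step 3: when the 20% limit is passed.** Assumptions: more than a week means 8 nights; the run lies wholly in follow-up; withdrawal takes effect on the last night of the run, d. The earliest is d = 30 + 8 = 38. The latest that loses any night is d = 59. That gives 22 possible nights.

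- 60-night base, only unrecorded nights missing: (60 − d)/60 > 0.20. At d = 47 it is 13/60 = 21.7%; at d = 48 it is 12/60 = 20.0%, not above the limit. Passed for d = 38 to 47, 10 of 22.
- 30-night follow-up base: (60 − d)/30 > 0.20. At d = 53 it is 7/30 = 23.3%; at d = 54 it is 6/30 = 20.0%. Passed for d = 38 to 53, 16 of 22.
- Counting the expected 18% quality exclusions as missing too, 60-night base: 1 − 0.82d/60 is 20.7% at d = 58 and 19.4% at d = 59, so 21 of 22.
- The same on the 30-night base: 1 − 0.82(d − 30)/30 is 20.7% at d = 59, so 22 of 22.

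The protocol does not say which base or which definition of missing applies. If quality exclusions count, full completers are caught as well: with X ~ Binomial(60, 0.18) and independent nightly losses, P(X ≥ 13) = 0.276. On that reading the exclusion is not special to safety withdrawals.

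These counts are calendar positions. They are not probabilities or a bias. They show that an early withdrawal passes the limit on every reading, while a late one depends on the reading.

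**Step 4: sensitivity of a comparison this small, under an assumed worst case.** Take no true effect, an unadjusted one-sided t test at 5%, 16 per arm, and the lowest scorers dropped from the experimental arm only, without replacement (20,000 simulated trials):

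| Dropped | Shift in difference | One-sided rejection |
|---|---|---|
| 0 | 0.00 SD | 5.1% |
| 1 | 0.12 SD | 10.2% |
| 2 | 0.22 SD | 16.5% |

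Nothing in the protocol says that removals would fall in one arm. The table shows only what one or two decisions can do at this size.

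**The case against.** The strongest reply is that this is a matter of one word. The Concomitant Care entry is a compressed list item without an auxiliary verb and may be shorthand for the full sentence in Incidental Findings. Clinical discretion over withdrawal is not in itself a design error. That is fair as far as it goes, but the two sections still give different instructions, and discretion matters more when the trigger is the endpoint and the arm is known.

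A second reply concerns timing. Withdrawal on the eighth low night needs near-daily review of scores, and no such schedule is stated. Adverse events are documented at baseline, day 30 and day 60, and outcomes are not analysed until completion. If a low run were noticed only at day 60, no nights would be lost. This stands, and it limits the calendar counts to an illustration.

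Third, the consent procedures are not shown and may say more about withdrawal and data retention. This also stands. They are not the analysis plan, however, and the protocol says that it contains all of that.

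A reader might infer that the protocol is silent on whether these participants stay in the analysis. It is not: the general rules on missing nights, insufficient data and deletion reach most early withdrawals. A reader might also infer that the protocol requires every safety withdrawal to be removed. It does not: the 20% rule is worded both as fixed and as optional, sufficient nights is undefined, and a late withdrawal may keep enough nights.

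**Conclusion.** The point holds and is minor. One safety trigger carries two consequences, it is the primary outcome variable, and the general rules would normally remove and replace a participant withdrawn early in follow-up because the outcome was poor. A late withdrawal is left unsettled.

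The size of any bias cannot be computed: the protocol gives no frequency of scores below 30 and no SD. The event is probably rare, since participants are healthy adults screened for sleep disorders, and Interpretation Guidance labels all findings preliminary. With 16 per arm, a single decision still changes who is compared.

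The conclusion rests on two readings: that a researcher-initiated withdrawal is not exempt from the missing-night rules (no exemption is stated), and that such a participant counts as one who needs to be excluded (natural, but not explicit). It would be going too far to conclude that the result will be biased towards the experimental arm. The Accountability Framework mentions watching that arm for worsening scores, so unequal detection is possible, but nothing shows that it occurs.

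**What to change.** State one rule in both Concomitant Care Protocol and Incidental Findings, for both arms: at more than one consecutive week below 30, refer the participant, let them stop following the advice, and ask them to keep wearing the watch to day 60 if willing. Log each crossing and each decision by arm.

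In Adherence Assessment, Data Collection Quality Control, the missing-data sentence and the deletion section, state that participants meeting this trigger are not excluded, replaced or deleted (unless they ask for deletion), and that all their recorded follow-up nights enter the as-randomised primary analysis. Add a sensitivity analysis without them.

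The cost is a few sentences and possibly ethics review under Protocol Amendments. Anyone who stops wearing the watch contributes a mean from few, mostly low nights (as few as 38 − 30 = 8). That can distort the participant's mean as well as widen the confidence interval, which is why continued wear is the first request. Recruitment ended in July 2025 and data collection was due to finish by December 2025. For participants already completed, only the analysis and retention rules can change, and only if their data still exist.

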#### Posttrial Care

There is no posttrial provision of interventions. Personalized recommendations are study-specific research interventions, not ongoing clinical care interventions. After study completion, participants may continue using strategies that helped them. There is no ongoing monitoring or intervention delivery. Participants are encouraged to consult health care providers for persistent sleep concerns. No direct medical benefits are guaranteed.

### Access Control and Protection Layers for Potential and Excluded Participants

Data collected from potential participants who do not fill out the informed consent form (Multimedia Appendix 3) or the commitment letter (Multimedia Appendix 4) and those who voluntarily withdraw or need to be excluded from the study are immediately and securely deleted.

### Access Control and Protection Layers for Enrolled Participants

Only the principal researcher has access to all study data, including identifiable information linking Participant_ID to personal information (mapping). The only risk is the mapping between the participant and the alias, which is kept in physical form at a secure physical location. Accessing it through a digital hacking attack is not possible. Participant data are stored securely and can be accessed only by authorized research personnel. Data will be retained for 5 years after publication, while the deidentified dataset will be retained indefinitely.

Data security involves (1) physical security (paper PSQI forms are stored in a locked filing cabinet at a secure location), (2) digital security (electronic files are password-protected and encrypted, and are stored on the researcher’s local computer only [no remote or cloud storage of identifiable data]), and (3) transmission security (Samsung device data download uses encrypted protocols [HTTPS]).

### Anonymization Process (Deidentification)

Anonymization involves assigning an alias to the personal data collected from each participant at different process steps. Email or Samsung accounts do not use personal data. These accounts are only used for data collection, as the approach is already anonymous by design.

An alias is used at each phase of the process. The smartwatch user setup is generic, and the smartwatch collects objective data without the participant’s personally identifiable data. The same device and setup are used throughout the study. The pairing device setup, like the user setup, is generic, and thus, the mobile phone collects objective data without the participant’s personally identifiable data. PSQI questionnaire data collection uses the Participant_ID alias for subjective data collection without the participant’s personally identifiable data. In the last phase, the data are merged into a single dataset, which is one of the research outputs.

### ML and AI Elements

Participants receive an explanation that the algorithms will analyze individual sleep patterns; a clarification that recommendations are statistically derived suggestions, not medical diagnoses; a statement that they retain full autonomy to follow or ignore recommendations; a description of SHAP explainability (plain-language explanations of personalized insights); and an assurance of human oversight (the researcher reviews all ML outputs before delivery).

### Enhanced AI/ML-Specific Consent Elements

Given the ML component, participants are explicitly informed about how ML models work (pattern recognition in their individual data) and what SHAP analysis means (identifying which factors predict their sleep scores). They are also informed that recommendations are correlational, not causal (eg, “REM correlates with higher scores” not “REM causes better sleep”), and that they have a right to question or decline any recommendation. Furthermore, they are told that the researcher reviews the recommendations before delivery (human-in-the-loop approach) and that no automated health decisions are made.

## Results

This protocol describes the planned analytical approach. The actual results, including group comparisons, effect sizes, statistical significance levels, and interpretation of findings, will be reported in a subsequent manuscript following study completion. The study is funded by Instituto Tecnológico y de Estudios Superiores de Monterrey (publishing fee) and *Secretaría de Ciencia, Humanidades, Tecnología e Innovación*, which was formerly called *Consejo Nacional de Ciencia y Tecnología* (wearable and pairing device equipment funding). The funding reference number is REF4661568-251121 (November 24, 2025). The trial has not yet been registered, but we intend to register it on ClinicalTrials.gov.

The study is currently in progress. Recruitment started in August 2024 and ended in July 2025. Data collection is expected to be completed by December 2025. The study will (1) compare 960 nights from the control group with 960 nights from the experimental group to explore whether ML interventions can improve sleep scores using wearable technology, (2) generate a dataset from objective data for iterative model training and analysis, (3) correlate objective and subjective sleep quality metrics, and (4) establish whether a feasible framework for proactive sleep quality approaches can be developed. The final analyzed results incorporating all quality control procedures, statistical analyses, and exploratory investigations will be available by March 2026, and the findings will be submitted for peer-reviewed publication within 6 months of study completion.

Upon completion of data collection by December 2025, the study will generate a comprehensive dataset from 32 participants (16 per arm) wearing Samsung Galaxy Watch 4 devices for 60 consecutive nights each, yielding approximately 1920 nights of sleep data. The final dataset will include 18 variables (Table 2).

**Table 2. T2:** Final variables included in this study.

Variable		Description	Unit	Data type
Explanatory variable				
Participant_ID		Unique number assigned to each participant	Number	Integer
Night_Number		Night count	Number	Integer
sleep_duration		Sum of N1, N2, N3, and REM^a^	Minutes	Integer
movement_awakening		Count of movement during sleep	Number	Integer
sleep_cycle		Count of sleep cycles	Number	Integer
mental_recovery		Score assigned according to the REM phase	Score (0‐100 scale)	Integer
physical_recovery		Score assigned according to the N3 phase	Score (0‐100 scale)	Integer
efficiency		real_total_sleep by sleep_duration	Percentage	Integer
Transition_N1		Sum of minutes of sleep in the N1 phase	Minutes	Integer
Light_N2		Sum of minutes of sleep in the N2 phase	Minutes	Integer
Deep_N3		Sum of minutes of sleep in the N3 phase	Minutes	Integer
REM		Sum of minutes of sleep in the REM phase	Minutes	Integer
real_total_sleep^b^		Sum of N2, N3, and REM	Minutes	Integer
Transition_pct		Percentage of sleep in the N1 phase	Percentage	Float
Light_pct		Percentage of sleep in the N2 phase	Percentage	Float
Deep_pct		Percentage of sleep in the N3 phase	Percentage	Float
REM_pct		Percentage of sleep in the REM phase	Percentage	Float
Target variable				
sleep_score		Score assigned for the night	Score (1‐100 scale)	Integer

a REM: rapid eye movement.

b The “real_total_sleep” variable excludes the N1 transition stage from total sleep duration, as this brief transitional period between wakefulness and consolidated sleep is typically excluded from restorative sleep calculations in sleep research.

The dataset will enable comparisons between the control group (960 nights; participants receiving generic sleep hygiene education on day 30) and the experimental group (960 nights; participants receiving personalized ML-derived recommendations on day 30).

Each night of sleep data will be automatically collected through sensors by Samsung Galaxy Watch 4 and processed through the manufacturer’s proprietary algorithms to generate objective sleep metrics. Data will be organized by participant identifier and temporal sequence to enable both group-level comparisons and individual-level ML model development.

Data completeness evaluation based on pilot testing and literature review suggests that approximately 18% of individual nights may be excluded due to the quality control criteria, with participant replacement ensuring that the final dataset achieves the target 1920 nights across all study participants.

